### Concealment mechanism {16b}

Only the unblinded member of the research staff will perform the randomisation procedure. The interface of eCRF will conceal subject treatment allocation to all other personnel involved in the study. Subject allocation report will be placed in an opaque sealed envelope into patients’ medical notes in care emergency unblinding is needed.

### Implementation {16c}

All newly admitted patients in each participating ICU will be screened daily for eligibility and recorded in a screening log in eCRF. All potentially eligible patients or their representatives will be approached by the site investigator and offered participation in the trial. Those consenting will be reported back to the unblinded member of research staff who will perform randomisation procedure and record baseline data in eCRF. All data will be recorded by site investigators into patients’ medical chart and by research nurses into a custom-built eCRF. Follow-up visits or phone calls will be performed by research nurses.

## Assignment of interventions: blinding

### Who will be blinded {17a}

The study medication will be prepared in each centre also by a dedicated unblinded member of research staff and handed over to the treatment team in an opaque syringe or mug, respectively, depending on whether the study medication is to be administered by mouth or into a nasogastric tube. Site investigators, research nurses and coordinators will be blinded to subjects’ treatment allocation. Study statistician will have access to subject treatment codes, but for the interim analysis, he will present processed data only labelled as “group X”, “group Y”, and “group Y”, without disclosing actual treatment allocation. The steering committee can ask for group unblinding if deemed necessary for the subject safety. Both REB and Czech Drug Agency (SUKL) will be notified about the decision to unblind groups in the report letters from interim analysis.

### Procedure for unblinding if needed {17b}

In case the investigator suspects that an adverse event had occurred that represents a threat to the patient’s safety, it is possible to unblind the study treatment allocation. An unblinded pharmacist will insert a card with patient’s treatment allocation into an opaque sealed envelope labelled “Emergency unblinding only, do not open” into the patients’ medical chart. The Principal Investigator must be notified about the use of emergency unblinding procedure within 24 h.

## Data collection and management

### Plans for assessment and collection of outcomes {18a}

Prior to initiation of each study site, the central research coordinator will train the local dedicated study personnel in the use of e-CRF and other study procedures. The medication will be delivered via a central pharmacy in sealed numbered boxes and stored in ICUs. Adhering to Good Clinical Practice rules and guidelines is of upmost importance despite all the challenges during the current pandemic situation. Nonetheless, the eCRF has been designed to balance the safe conduct of the clinical trial and feasibility of timely data entry during staff shortages and overload. In order to do so, all data that is not essential for safety can be input in retrospect. Data on interventions that we know/think influence survival will be monitored and described. This includes concomitant antiviral antimicrobial diagnosis. We will also collect data on how the respiratory specimen for rtPCR diagnostic was collected (smear, endotracheal aspirate, bronchoalveolar lavage). It is likely that most patients will have complete per-protocol data sets whilst in ICU as in critically ill patients most data are recorded as a part or routine care.

### Plans to promote participant retention and complete follow-up {18b}

Day 28 and 90 follow-ups will be performed as physical visit in hospitalised patients or a telephone interview. Vital status, mechanical ventilation status and whether the patient is still in ICU and in hospital are all very robust data that can be obtained with minimum equipoise even over the phone. In addition, the protocol recommends that patient’s self-reported data are checked against hospital notes and/or clinical information system.

### Data management {19} and confidentiality {27}

All data will be stored in password-protected, custom-programmed Oracle-based database linked to eCRF and stored and backed-up in secured servers located within hospital premises. Primary imputation of data into the eCRF will be performed by investigators or a dedicated study personnel under the supervision of investigators. Investigators vouch for source data quality and integrity.

For the sake of all analyses as well as for storage of raw data in a public database, record-level patients’ data will be de-identified as per local legislation.

### Plans for collection, laboratory evaluation and storage of biological specimens for genetic or molecular analysis in this trial/future use {33}

Due to the pragmatic nature of the study, laboratory investigation is minimised to a minimum required for assessing safety. In all patients, only 3 plasma samples will be stored for exploratory analyses described above. We plan to dispose all samples after the analysis. No molecular analyses of human DNA are planned.

## Statistical methods

### Statistical methods for primary and secondary outcomes {20a}

The proportion of patients alive and off mechanical ventilation (primary outcome) between intervention and control groups will be calculated using chi-square test. *p* value is adjusted for multiple comparisons to *p* = 0.017 as there are 3 comparisons between 3 study arms. Survival and ICU/length of stay will be compared using Kaplan-Maier’s curves and exploratory analyses my multi-level regression using statistical packages in software in R. We plan to analyse the primary outcome separately in patients who require mechanical ventilation at baseline from those who do not and we in patients above or below 70 years of age as a priori subgroup analyses.

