## Interventions

### Explanation for the choice of comparators {6b}

At present, there is no effective drug to treat COVID-19 and hence best supportive care in addition to randomising patients into high quality RCTs is recommended by World Health Organization [7], Infectious Diseases Society of America [8], Surviving Sepsis Campaign Guidelines endorsed by European Society of Intensive Care Medicine [9], and Czech Society of Intensive Care Medicine (www.csim.cz). All patients will receive best supportive care that will be monitored, but not protocolized. It is recognised that the standard of care may substantially differ among study centres and that is why randomisation is stratified. Concomitant medication may include off label use of unproven treatments, but not participation in another outcome-based interventional trial.

Hence, the administration of a placebo in addition to best supportive care will be used in the control group.

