### Sample size {14}

Based on data from Wuhan [6] and Washington [7], where 67% of patients had died within 2 weeks and half of the survivors needed protracted mechanical ventilation, we assume the incidence of the primary outcome in the control group (i.e., being alive and off the ventilator in 2 weeks) to be 25%. The study gives us 80% chance to detect the increase of the primary outcome to 50% in one or both interventional groups at *p* < 0.017 with 74 patients in each arm. In order to compensate for drop-out and loss of follow up, we plan to enrol 240 subjects into the study. No replacement of subjects who dropped out from the study is planned.

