## Assignment of interventions: allocation

### Sequence generation {16a}

Randomisation procedure will be performed in blocks of 6 and stratified for study centre and age (> 70 or ≤ 70 years). Electronic Case Record Form (eCRF) will perform randomisation using random sequence script in software R and generate medication code. Rationale: Patient’s age is the single most powerful predictor of outcome and stratifying randomisation and stratification decreases the probability of treatment groups being of different age at baseline by chance. In analogy, study centres may vary in the use of non-protocolised treatments, which could bias the results. Randomisation blocking and stratification are described in the protocol and hence will not be concealed for study site investigators, but the computer-generated randomisation sequence will be concealed for all study personnel but the statistician (PW). This prevents any predictability of treatment allocation for subjects before randomisation.

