### Methods for additional analyses (e.g., subgroup analyses) {20b}

We plan to analyse the primary outcome separately in patients who require mechanical ventilation at baseline from those who do not and we in patients above or below 70 years of age as a priori subgroup analyses.

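### The primary test is an unadjusted chi-square although randomisation is stratified by centre and age and baseline ventilation is recorded: valid, but it gives up an amount of power that depends on unstated prognostic strength

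*Protocol article*

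**What the plan says.** Statistical methods for primary and secondary outcomes {20a} sets the primary test: "The proportion of patients alive and off mechanical ventilation (primary outcome) between intervention and control groups will be calculated using chi-square test". The threshold for the *p* "value is adjusted for multiple comparisons to *p* = 0.017 as there are 3 comparisons between 3 study arms". The only regression mentioned there is multi-level, labelled exploratory, and stands in the sentence on survival and length of stay.

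Sequence generation {16a} says randomisation is "stratified for study centre and age (> 70 or ≤ 70 years" in blocks of 6. Its stated reason is that "age is the single most powerful predictor of outcome" and that centres may vary in treatments the protocol does not prescribe. Explanation for the choice of comparators {6b} gives the same reason for centre: "the standard of care may substantially differ among study centres and that is why randomisation is stratified".

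Baseline ventilation status is not a stratification factor. It does define a secondary outcome (Secondary outcomes, under Outcomes {12}) and a subgroup: Methods for additional analyses {20b} plans to "analyse the primary outcome separately in patients who require mechanical ventilation at baseline from those who do not".

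**The concern.** The design treats age and centre as prognostic and the primary test then ignores both. When allocation is balanced on a prognostic factor, a test that ignores it uses a variance that is too large for the difference it examines. It therefore rejects slightly less often than its nominal level and loses some power.

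Baseline ventilation is the more important covariate. Patients may enter ventilated or not, and the endpoint is being alive and off ventilation at day 14, so status at entry is close to a baseline value of the endpoint. Neither the randomisation nor the primary test protects against a chance imbalance in it.

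The Discussion acknowledges that power is relatively low. An adjustment that uses data already collected is worth having in that setting, provided its benefit is stated no more strongly than the document allows.

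**Working it through.** **1. The plan's own figure.** Inputs from Sample size {14}: "we assume the incidence of the primary outcome in the control group (i.e., being alive and off the ventilator in 2 weeks) to be 25" per cent, and "80% chance to detect the increase of the primary outcome to 50% in one or both interventional groups at *p* < 0.017 with 74 patients"; the 74 is per arm. Sidedness is not stated; two-sided is assumed because a chi-square is planned. The normal quantiles are 2.387 (0.017 two-sided) and 0.842 (80% power).

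- Unpooled formula: n = (2.387 + 0.842)² × (0.25×0.75 + 0.50×0.50) / 0.25² = 10.42 × 0.4375 / 0.0625 = 72.95, so 73 per arm. The stated 74 reproduces.
- Power of the pooled test at 74: Φ[(0.25 − 2.387 × √(2×0.375×0.625/74)) / √(0.4375/74)] = Φ[(0.250 − 0.190)/0.0769] = Φ(0.78) = 78.3%. Simulation gives about 79%.

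**2. Inputs the document does not give.** It states no share ventilated at baseline, no association of ventilation or age with the outcome, and no R². These are assumed below and shown as a range.

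**3. Gain from adjusting for baseline ventilation.** Simulation with 74 per arm, overall rates of 25% and 50%, a common treatment odds ratio and two-sided alpha 0.017. It compares the Pearson chi-square with a two-stratum Cochran-Mantel-Haenszel (CMH) test, 60,000 trials per scenario in the first two numeric columns. The odds ratio is that of the control-group success rates; for example 40% against 10% gives (0.40/0.60)/(0.10/0.90) = 6.

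| Ventilation odds ratio | Chi-square, half ventilated | CMH, half ventilated | Gain with 30–70% ventilated |
|---|---|---|---|
| 1.5 | 78.9% | 78.6% | about 0 |
| 2 | 79.0% | 79.6% | 0 to 1 |
| 3 | 78.7% | 81.0% | about 2 |
| 4 | 78.4% | 82.4% | 3 to 4 |
| 6 (10% vs 40%) | 78.8% | 85.2% | 4.5 to 6.5 |
| about 15 (5% vs 45%) | 78.6% | 91.5% | 7 to 13 (odds ratios 10–15) |

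The lower ends belong to 30% ventilated and are good to about a point: a re-run with 200,000 trials gave gains of 2.7, 4.4 and 6.3 there at odds ratios 4, 6 and 10.

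**4. Age, alone and with ventilation.** A separate simulation (5,000 to 8,000 runs, error about 0.5 point per power figure) balanced allocation within centre and age and compared the chi-square with a logistic likelihood-ratio test.

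- Age alone, 30% over 70: 79.1% to 80.2% at odds ratio 2, and 79.6% to 81.4% at 3. The largest gain tried was 79.6% to 84.9%, at odds ratio 5 with half over 70.
- Ventilation and age together, half ventilated: odds ratios 2 and 2, 78.9% to 81.1%; 3 and 3, 78.8% to 83.9%; 4 and 3, 78.8% to 84.8%; 10 and 3, 79.0% to 90.4%.
- With neither factor prognostic: chi-square 79.0%, logistic 79.4%, four-stratum CMH 78.1%. Adjusting for useless covariates can therefore cost the CMH test up to about a point.

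**5. Type I error.** With a two-level factor balanced between arms, the chi-square rejects at about 1.7% for an odds ratio of 2, 1.5% for 3 and 1.4% for 4. With age and centre balanced, age odds ratio 3 and ventilation odds ratio 4 (not balanced), it rejected at 1.4% in 6,000 runs; the simulation error there is √(0.017×0.983/6000) = 0.17 points.

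**6. Limit on stratifying by everything.** 8 sites × 2 age groups × 2 ventilation states = 32 cells. One comparison has 2 × 74 = 148 patients, and 148/32 = 4.6 per cell.

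**The case against.** A reader might infer that the chi-square throws away at least 6 points of power. The document does not support that as a floor. It gives no prognostic strength, and 6 points needs a ventilation odds ratio of about 6 with about half or more of patients ventilated, or about 4 combined with an age odds ratio of 3. At odds ratios of 2 to 3 the gain is about 0 to 2 points for ventilation alone and about 2 to 5 for both factors together. The larger gains also come from ventilation, which is not a stratification factor, so they cannot be attributed to ignoring the stratification.

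A reader might also infer a true error rate of 0.7 to 1.2%. That requires a balanced factor with an odds ratio of 6 to 15. Ventilation is not balanced by design, and for age at odds ratios of 2 to 4 the conservatism is mild.

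Other points in the plan's favour:

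- The chi-square is valid, does not inflate false positives and matches the sample-size calculation. This stands.
- The trial is described as exploratory, and the subgroup analyses by ventilation and age would make an imbalance visible. This stands, but they would not remove it from the primary estimate.
- Covariate detail is commonly left to the analysis plan, which is not shown. This does not answer the point, because the protocol has already named the test.
- The trial is recruiting, changes need ethics and regulatory review, and the statistician has access to treatment codes. This stands as a cost and makes timing important.

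**Conclusion.** The point holds as a matter of efficiency and consistency with the design, not of validity. The primary test ignores two factors the protocol itself calls important and a third, baseline ventilation, that is likely to be closely tied to the endpoint.

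The power recoverable runs from essentially nothing to about 13 points, as tabulated, and the document does not allow a single figure. A sizeable gain is plausible because ventilation status is part of the endpoint, but it remains an assumption. The figures assume two-sided alpha 0.017, 74 analysed per arm, 30 to 70% ventilated at entry and no interaction between treatment and covariate. The ventilation figures are for a two-stratum test and the age figures for a logistic model without centre; neither describes a model that also includes centre.

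**What to change.** Before any unblinded comparison, and so before the interim analysis at the 120th subject, name as the primary analysis one of the following:

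- a Mantel-Haenszel test stratified by age group and baseline ventilation; or
- a logistic regression on the same two factors, reported as a standardised risk difference.

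Handle centre sparingly, by pooling small sites or using a random intercept, because full cross-stratification leaves under 5 patients per cell. Use the same test at the interim analysis, keep the chi-square as supportive, and describe the power gain as conditional on prognostic strength.

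The cost is a protocol amendment with its ethics and regulatory review. No extra patients or data are needed. If the covariates prove only weakly prognostic there is essentially no gain, with a loss of up to about one point for the stratified test.

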## Objectives {7}

The primary study objective is to test the hypothesis that early administration of combination therapy slows disease progression and improves mechanical ventilation-free survival.

The secondary (exploratory) study objective is to investigate whether the intervention decreases the viral load and influences oxygenation and mechanical feature of the lung.

SPIRIT guidance: Specific objectives or hypotheses.

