## Trial design {8}

Prospective, randomised (1:1:1), placebo and active-comparator controlled, parallel group, double-blind exploratory trial.

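### Testing all three pairs of arms at a flat 0.017 is valid, but at 74 per arm it gives up about 6 to 8 points of power per active-versus-control comparison that a three-arm step-down recovers

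*Protocol article*

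**What the plan says.** Trial design {8} describes a "Prospective, randomised (1:1:1), placebo and active-comparator controlled, parallel group, double-blind exploratory trial". Objectives {7} names one primary hypothesis, that "early administration of combination therapy slows disease progression and improves mechanical ventilation-free survival".

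Statistical methods {20a} says that the primary outcome "between intervention and control groups will be calculated using chi-square test". The p value "is adjusted for multiple comparisons to *p* = 0.017 as there are 3 comparisons between 3 study arms", so the third pair, HC-A versus HC, counts in the adjustment alongside the two comparisons with control.

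Sample size {14} uses the same threshold. It assumes 25% in the control group and claims an "80% chance to detect the increase of the primary outcome to 50% in one or both interventional groups at *p* < 0.017 with 74 patients" per arm, with 240 enrolled to cover losses. Interim analyses {21b} uses 0.017 again as the efficacy criterion. No stepwise, closed or gated procedure is described.

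**The concern.** Bonferroni at 0.05/3 protects against three true null hypotheses at every step. In a three-arm trial that protection is needed only while all three arms may be equal. Once any two arms are shown to differ, at most one of the other two pairwise nulls can still be true. Keeping all tests at 0.017 after that point buys no protection that a 5% family-wise error requires, and it costs power.

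That matters here because the Discussion itself calls the power relatively low. The threshold is also written into both the analysis and the sample size, so it is a fixed design choice and not a detail left to a later analysis plan.

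**Working it through.** **Inputs.** Control 25%, active 50%, 74 per arm, 80% power and threshold 0.017 come from {14}. The three pairwise comparisons and the chi-square test come from {20a}. The total of 240 (80 per arm) comes from {14}. A two-sided test and a 5% family-wise level are assumed; the latter is implied by 3 × 0.017 ≈ 0.05.

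**The protocol's own figure.** With the unpooled normal formula, n = (z₁₋α/₂ + z₀.₈)² × [p₁(1−p₁) + p₂(1−p₂)] / (p₂−p₁)². At α = 0.05/3 this is (2.394 + 0.842)² × (0.1875 + 0.25) / 0.0625 = 73.3, rounded up to 74. The stated size reproduces. The pooled formula gives 77 at 0.017 and 78 at 0.05/3. The exact power of the Pearson chi-square at 74 per arm and 0.017 is 78.7%.

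**Why three arms are special.** The nulls are C = HC, C = HC-A and HC = HC-A. If any two hold, so does the third. Every intersection of two or more is therefore the global null, and two procedures follow:
- *Shaffer's step-down:* compare the smallest p with 0.05/3; if significant, test the other two pairs at 0.05 each.
- *Closed test:* overall 2-df chi-square at 0.05; if significant, test each pair at 0.05.

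**Power per active-versus-control comparison where the active rate is 50%** (exact enumeration of three binomials, Pearson chi-square; rates in the order C/other active/active):

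| n per arm | Rates (%) | Flat 0.017 | Shaffer | Closed |
|---|---|---|---|---|
| 74 | 25/25/50 | 78.7% | 85.2% | 87.2% |
| 74 | 25/50/50 | 78.7% | 84.8% | 86.4% |
| 80 | 25/25/50 | 82.7% | 87.8% | 89.4% |
| 80 | 25/50/50 | 82.7% | 88.4% | 89.2% |
| 74 | 25/37.5/50 (assumed) | 78.7% | 79.4% | 81.2% |

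The gain at 74 per arm is 6.1 to 6.5 points with Shaffer and 7.7 to 8.5 with the closed test. At 80 per arm it is 5.2 to 5.8 and 6.5 to 6.7 points. Plain Holm gains only about 2.4 points at 74 per arm.

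**Other definitions of success, both active arms at 50%, 74 per arm.**
- At least one arm better than control: 90.2% flat, 89.9% Shaffer, 91.7% closed.
- Both arms better than control: 67.1% flat, 79.6% Shaffer, 81.2% closed.

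**Family-wise error, single final look.**
- Global null, 74 per arm: the closed test gives 5.0% (all rates 25%) and 5.2% (all 50%); flat 0.017 gives 4.7% and 4.4%.
- Both active arms at 50%, 74 per arm: the error on the one true null is 5.8% for either new procedure. This is discreteness of the chi-square, since an unadjusted 0.05 test gives about the same. At 80 per arm it is 4.8%.

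**Lost rejections.** Shaffer never rejects less than Bonferroni at exactly 0.05/3. The protocol's 0.017 is that figure rounded up, which explains the 0.3-point deficit above (90.2% against 89.9%). With the closed test, a pairwise p below 0.017 fails the overall gate in under 1% of trials in every scenario tabulated.

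**The case against.** The strongest reply is that nothing here is wrong. Bonferroni is valid, prespecified and consistent with the sample size. That stands: a reader might infer that the analysis is invalid or its threshold miscalculated, and the documents do not support that.

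A second reply is that the stated power is already met. A reader might take 78.7% against 80% as a shortfall, but the gap comes from the variance formula, and 80 per arm with full retention gives about 82.7%. This also stands, and it reduces the gain to between 5 and 7 points.

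Third, the gain depends on what counts as success. The sample-size wording, "in one or both interventional groups", can be read as finding at least one effective arm. If both work, the closed test adds only about 1.5 points on that reading and Shaffer adds nothing. For HC-A versus C with HC halfway between, at 37.5%, the gain is about 1 to 2.5 points. So it would be wrong to infer that every real effect then exceeds 80% power: HC versus C at 25% against 37.5% reaches only about 37%.

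Fourth, 5% family-wise error should not be read as holding for the trial as a whole. The interim criterion in {21b} reuses 0.017. If it is acted on, simulation with 40 then 80 per arm puts the error at about 7.5–7.9% with the flat rule and 7.9–8.3% with a closed final test. The problem exists under either procedure and has to be settled on its own.

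Finally, Bonferroni gives simple simultaneous intervals and the alternatives do not. That is a real but small cost. What survives all of this is a material gain under the protocol's own planning alternatives.

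**Conclusion.** The point holds as lost efficiency. Under the alternatives in {14}, power per active-versus-control comparison at 74 per arm rises from 78.7% to about 85% (Shaffer) or 86–87% (closed), and at 80 per arm from about 82.7% to 88–89%, with no additional patient. These figures assume two-sided Pearson tests, equal arms, a control rate of 25% and an active rate of exactly 50%. The statement that family-wise error is about 5% covers one final look and is subject to chi-square discreteness. The change is worth making because it is nearly free, but results obtained under the present rule would still be valid.

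**What to change.** In {20a}, replace the flat 0.017 by Shaffer's step-down: the smallest of the three pairwise p values against 0.05/3 and, if significant, the remaining two each at 0.05. The closed test (overall three-group chi-square at 0.05, then each pair at 0.05) is the alternative if slightly more power is preferred and an occasional loss at the gate is acceptable. Name one of the two, before any unblinded outcome data are seen, and restate the power in {14} for it.

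The cost is two sentences in {20a}, a revised power statement and a short note on intervals: 98.3% Bonferroni intervals (1 − 0.05/3) can still be reported alongside, with a remark that they may not match the step-down decisions exactly. Arms, outcome and sample size do not change. The interim threshold in {21b} should be resolved separately before 5% is claimed for the whole trial.

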Chloroquine has been used for malaria treatment and chemoprophylaxis, and hydroxychloroquine is used for the treatment of rheumatoid arthritis, systemic lupus erythematosus and porphyrias. Both drugs have in vitro activity against SARS-CoV, SARS-CoV-2 and other coronaviruses, with hydroxychloroquine having relatively higher potency against SARS-CoV-2 known to be susceptible in vitro to exposure to hydroxychloroquine [2–4]. At the moment, clinical trials are ongoing to test clinical efficacy in pre- and post-exposure prophylaxis in SARS-CoV-2. In one highly cited French non-randomised observational study by Gautret et al., a significant reduction of virus carriage has been observed in patients coincidentally treated by azithromycin in addition to hydroxychloroquine [5] as a part of initial empirical therapy of community-acquired pneumonia. Azithromycin is a macrolide antibiotic, which binds to the 50S subunit of the bacterial ribosome, thus inhibiting translation of mRNA. The positive-sense RNA viruses and indeed all genes defined as positive-sense can be directly accessed by host ribosomes to immediately form proteins and the effects of azithromycin on this process are not known. No data are available at present on the clinical efficacy of hydroxychloroquine alone or in combination with azithromycin, and it is likely that any treatment affecting virus replication would only be effective if administered early, before overt ARDS develops.

In the light of this, we designed a trial in which we test a hypothesis that early administration of hydroxychloroquine alone or in combination with azithromycin can prevent respiratory deterioration in patients admitted to intensive care due to rapidly progressive COVID-19 infection.

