### Intervention description {11a}

All study medication is provided as a kind gift of Zentiva, ltd. Unblinded study pharmacist will prepare 40 ml of sterile water study medication, according to patient’s allocation into the treatment arm:
Hydroxychloroquine sulphate 200 mgAzithromycin dihydrate 500 mgLactose as placebo

For possible drug-drug interactions and details of possible adverse effects, see Summary of Product Characteristics for both investigational medicinal products.

Treatment group allocation is as follows (Table 1):

**Table 1 Tab1:** Treatment allocation in 3 study arms

Study group		
HC-A (Intervention)	Azithromycin	Hydroxychloroquine
HC (ACTIVE COMPARATOR)	Lactose	Hydroxychloroquine
C (PLACEBO)	Lactose	Lactose

Each study subject will be given:
Day 1: Patients receive two doses 400 mg of hydroxychloroquine or placebo in 12 h interval and 500 mg of azithromycin or placebo once in 24 h (with the first dose of hydroxychloroquine or placebo)Days 2–5: Patients receive two doses 200 mg of hydroxychloroquine or placebo in 12 h interval 250 mg of azithromycin or placebo once in 24 h (with the first dose of hydroxychloroquine or placebo)

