### Interim analyses {21b}

We plan to perform an interim analysis after the primary outcome is known for the 120th subject. As mentioned above, primary and secondary outcomes will only be calculated in patients with confirmed COVID-19 infection who received at least one dose of IP. Adverse events will be calculated in all randomised patients (intention-to-treat analysis).

All suspected unexpected serious adverse events (SUSARs) will be reported to both REB and to the steering committee, who may decide to stop the trial for safety concerns. Apart from safety, other reasons for stopping the trial are as follows:
Emergence of new data (e.g., publication of the results of a big RCT) that may lead the continuation of the trial unethical. This may be due to safety concerns of the placebo group (in case a strong clinical benefit is proven by other trials) or any of the interventional groups (e.g., if harm is reported by other trials). This rule also applies for emergence of a new treatment.After interim analysis: The steering committee will review primary outcomes and the summary of adverse events in all 3 groups (labelled as A, B, and C) whilst still blinded to treatment allocation. The treatment can be stopped if the following criteria are fulfilled:There is a significant difference in the primary outcome at *p* < 0.017 in between the groups.Futility: The futility criterion is not binding for the steering committee. Based on available data, the study statistician calculates the probability of being able to prove the null hypothesis with achieving the target number of subjects and the probability of type II error made by stopping the trial prematurely.Safety: In case the number of adverse events in one or more treatment groups is found uneven or unacceptably high.Details of pharmacovigilance are described in a dedicated section below.

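### The protocol does not settle which comparison answers its primary question: the objective, hypothesis, power statement, test plan and interim criterion point to different contrasts

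*Protocol article*

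**What the plan says.** Arms: HC-A (hydroxychloroquine plus azithromycin), HC (hydroxychloroquine plus placebo), C (double placebo). All references are to the Protocol article.

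- **Objectives {7}:** the primary hypothesis is that "early administration of combination therapy slows disease progression and improves mechanical ventilation-free survival". This is one regimen, HC-A.
- **Intervention description {11a}, Table 1:** only HC-A is labelled as the intervention. The next row reads "HC (ACTIVE COMPARATOR".
- **Background and rationale {6a}:** the hypothesis is that "early administration of hydroxychloroquine alone or in combination with azithromycin can prevent respiratory deterioration". This is two regimens. The Abstract says the same.
- **Sample size {14}:** the study is powered "to detect the increase of the primary outcome to 50% in one or both interventional groups". HC now counts as interventional. The level and the size per arm are given as "< 0.017 with 74 patients in each arm".
- **Statistical methods {20a}:** the primary outcome "between intervention and control groups will be calculated using chi-square test", which suggests contrasts against control. The next sentence sets alpha at 0.017 "as there are 3 comparisons between 3 study arms", a count that must include HC-A vs HC. No contrast is ranked.
- **Interim analyses {21b}:** one stopping criterion is met if "There is a significant difference in the primary outcome at" p < 0.017 between groups. Neither the contrast nor its direction is named, and the committee sees arms labelled only A, B and C.

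**The concern.** A Bonferroni split limits the chance of any false rejection. It does not define which rejection means that the primary objective was met. On this text, HC beating placebo meets the hypothesis in {6a} but not the objective in {7}. HC-A differing from HC, with neither separated from placebo, meets no stated hypothesis, yet it is one of the three counted tests and satisfies the interim criterion.

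Two things are at stake. The contrast that carries the main conclusion could be chosen after the data are seen. Enrolment could also end on an active-versus-active difference, with the placebo-controlled question open at about 40 per arm. These are statements in the article that disagree with one another, so an analysis plan could add detail but could not make them agree without overriding one of them.

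**Working it through.** **Inputs.** From {14}: control rate 25%, target 50%, 80% power, 0.017, 74 per arm. From {21b}: interim at 120 subjects, so 120/3 = 40 per arm under 1:1:1 allocation if all are analysable. Assumed: two-sided tests, uncorrected chi-square, and any HC rate other than 25% or 50%.

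**Step 1: reproduce the plan's sample size.** For one contrast, with unpooled variance:

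n = (z(1−α/2) + z(0.80))² × [0.25×0.75 + 0.50×0.50] / 0.25²

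With α = 0.05/3: (2.394 + 0.842)² × 0.4375/0.0625 = 10.47 × 7 = 73.3, so 74 per arm. The figure reproduces as a calculation for **one** active-versus-control contrast. Exact power of the uncorrected chi-square at 74 per arm and 0.017 is 78.7% (78.3% by the pooled normal formula).

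**Step 2: what the 80% covers.** Simulation, 1,000,000 trials, C 25%, HC 50%, HC-A 50%, 74 per arm:

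| Event | Probability |
|---|---|
| A given placebo contrast significant | 79% |
| Both significant | 67% |
| At least one significant | 90% |

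Check: 78.7 + 78.7 − 67.1 = 90.3. If both arms reach 50%, neither the chance of at least one success nor the chance of two is 80%.

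**Step 3: error rate.** With all arms at 25% and 74 per arm, at least one of the three tests is significant in about 4.6% of trials. The split works at the final look.

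**Step 4: HC-A vs HC as the only significant contrast at the interim.** C 25%, HC-A 50%, 40 per arm:

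| Assumed HC rate | HC-A vs HC alone meets the criterion |
|---|---|
| 25% | 15.9% |
| 35% | 3.1% |
| 40% | 1.0% |
| 50% | 0.1% |

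**Step 5: any contrast significant without HC-A vs C.** Same C and HC-A rates, HC at 25%, 35%, 40% and 50%: 12.0%, 2.4%, 2.6% and 11.6% at 74 per arm; 16.7%, 4.3%, 4.6% and 16.6% at 40 per arm. At HC 50% nearly all of these are HC vs C, which is on target under {6a} though not under {7}.

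**Step 6: does 74 per arm support a clearer choice?** One decisive contrast at 0.05 has about 89% power. Two placebo contrasts at 0.025 each have 82.4% power per contrast. One decisive contrast kept at 0.017 stays near 79%.

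**The case against.** The strongest reply is that the protocol mostly points one way. {20a} speaks of intervention against control, {14} of interventional groups, and the Abstract and {6a} include hydroxychloroquine alone. On that view {7} is one loosely worded sentence, HC vs C is a legitimate primary question, and the count of three only justifies a conservative alpha. Familywise error is held at the final look, the trial design section calls the trial exploratory, and {21b} permits stopping without requiring it, the decision resting on a committee vote ({5d}).

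Much of this stands. Nothing makes {7} control over {6a}, so an HC-versus-placebo result cannot simply be called off-target. What remains is that {7} and Table 1 do say something narrower, that the count of three needs HC-A vs HC, and that the interim criterion excludes no pair. The exploratory label does not settle it, because the Abstract describes the trial as designed and powered for its clinical question.

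A reader might infer something stronger: that the trial will usually be declared positive on the wrong contrast. With HC at 50% and HC-A at 25%, some contrast is significant in 91% of trials and HC-A vs C in 1.8%; with HC-A at 40%, some other contrast succeeds without HC-A vs C in 47%. Both cases need azithromycin to weaken the hydroxychloroquine effect, whereas the Abstract and the comment on the primary outcome in {12} expect it to strengthen it. They are not a fair measure of the problem.

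**Conclusion.** The inconsistency is real and should be resolved before outcome data are seen; recruitment was already open. It concerns which question is answered. It is not a sample-size error, since 74 per arm reproduces, nor a failure of error control at the final analysis.

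Its size depends on the HC rate. HC-A vs HC alone meets the interim criterion in about 16% of trials if HC equals placebo and HC-A reaches 50%, and in about 3% or less if HC is at 35% to 50%. With HC-A at 50% and HC between 25% and 50%, a contrast other than HC-A vs C is the only route to significance in about 2% to 12% of final analyses and 4% to 17% of interims. These figures assume two-sided uncorrected chi-square tests and equal arms.

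A reader might also take the 23% of trials in which exactly one placebo contrast succeeds, when both arms are at 50%, as trials that miss the objective. About half of those succeed on HC-A vs C and so meet {7}; the other part is about 11.5%.

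**What to change.** 1. **{7}, {6a}, {14}, {20a}:** choose one reading. Either widen {7} to name HC-A vs C and HC vs C as the two primary contrasts, or state in {20a} that HC-A vs C alone decides the objective and HC vs C is secondary.
2. **Under either choice:** make HC-A vs HC a secondary comparison that cannot by itself support a success claim or meet the efficacy criterion in {21b}.
3. **{21b}:** keep both placebo contrasts, in either direction, in the interim review. Tying the criterion to HC-A vs C alone would lose the primary-outcome signal if HC did worse than placebo.
4. **{14}:** state that the 80% is power for a single active-versus-control contrast (about 79% at 74 per arm), with about 90% for at least one and 67% for both if both arms reach 50%.

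**Cost:** wording only, with no extra patients or data. A significant HC-A vs HC result alone could no longer be claimed as primary success. If one contrast is made decisive but kept at 0.017, its power stays near 79% where 0.05 would give about 89%. Because the committee sees coded arms, the statistician, who holds the treatment codes ({17a}), would have to apply the placebo-contrast criterion; naming the pair that met it could reveal which arm is placebo, so the form of that report should be agreed in advance.
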